### Documentation, monitoring, and data management

All clinical data entered by the site staff into eCRFs will be recorded in a pseudonymized form exclusively using the patient’s identification code.

The Clinical Trial Centre Leipzig (ZKS Leipzig) will be responsible for trial monitoring. Pre-study, initiation, interim, and close-out visits will be performed in all centers. During the visits, the monitor will: (a) check informed consent forms of all patients enrolled, (b) perform targeted source data verification for patients with possible deviations, (c) perform source data verification of the key data in a random sample of at least 40% of the site’s patients (d) discuss open queries raised by data management or safety personnel check and update the investigator site file.

For creation of the trial database, the EDC tool secuTrial®, developed and distributed by interActive Systems GmbH (iAS), will be used. The information entered into the eCRF by an authorized member of the trial team will be systematically checked for completeness, consistency, and plausibility. The site staff is responsible for data correction and can resolve queries directly in the eCRF-page. During the whole course of the trial, daily backups of the data are made. Unauthorized access to patient data is prevented by the access concept of the trial database, which is based on a strict hierarchy and role concept. Any change of data is recorded automatically via audit trail within the database. At the end of the trial, once the database has been declared complete and accurate, the database will be locked.

### Safety aspects and data safety monitoring board

The exclusion criteria of this trial include all contraindications for the application of tDCS (e.g., metal plates or electronic implants in the brain or skull, skull defects, history of epileptic seizures, cardiac pacemaker). In addition, major depressive disorder (MDD) severity and suicide risk will be measured during treatment and follow-up visits with the BDI-II due to the theoretical risk of worsening or new development of depressive symptoms. This risk arises as the electrode placement in our study is opposite to the usual placement in depression treatment.

Information on adverse events (AEs) and serious adverse events (SAEs) will be collected during treatment period and up to the first follow-up visit after treatment period. (S)AE will be followed up until complete recovery and/or patient’s status is stable. A Data Monitoring Committee (DMC), consisting of three independent experts without conflicts of interest, will meet periodically to perform a review of the accumulated study data regarding the safety of the trial intervention as well as the integrity and validity of the data.

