It is still unknown how long any improvement of ADHD symptoms lasts after applying tDCS. A few studies support the hypothesis of a lasting effect of tDCS with improved clinical symptoms beyond the end of stimulation. In children and adolescents, 20–30 min anodal stimulation over the left DLPFC for five days yielded superior results in the stimulation group, as compared to sham as assessed by neuropsychological [24, 25] and clinical measurements [24, 25]. The latter study describes lasting clinical effects, which were most prominent 7 days after the stimulation. Notably, there is evidence that tDCS application over multiple days increases the duration of its beneficial effects to several weeks [26–29], although these studies were not conducted in patients with ADHD. Examining persisting effects of tDCS on ADHD symptoms in adult patients, Cachoeira et al. [30] found strong effects (Cohen’s *d* > 1) in a pilot study (*N* = 17) concerning inattention, and moderate ones concerning hyperactivity/impulsivity two weeks post-intervention (p.i.). Four weeks p.i. the effect size in regard to inattention was moderate compared to sham stimulation, supporting the hypothesis of a lasting effect of tDCS with improved clinical symptoms beyond the end of stimulation. In their randomized controlled pilot study, 20 min anodal stimulation of the right DLPFC over five consecutive days was applied, with similar placement and time regimen in the sham group. In data obtained in our own working group we found further justification for active electrode placement on the right side [31]. In a [11C] MRB-PET/MRI study with adult ADHD patients, we found lower noradrenaline transporter availability in right than in left prefrontal-thalamic regions, which may indicate that prefrontal hypo-activation is more pronounced on the right side, justifying anodal tDCS stimulation on the right DLPFC.

Given some evidence of clinical and cognitive improvements with anodal tDCS over the right DLPFC, the main objective of this clinical trial is to systematically test the efficiency of anodal tDCS over the right DLPFC in reducing ADHD symptoms when used as an alternative or add-on therapy to stable ongoing treatment compared to sham stimulation. We hypothesize that the benefits will persist for at least two weeks after the end of the stimulation. Our stimulation protocol is based on the pilot study by Cachoiera et al. [30], which showed promising results in a small sample.

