**Fig. 1 Fig1:**
[figure not shown]
Study timeline

During the follow-up phase, five visits are scheduled at day 7, 14, 28, 56, and 90 after the end of treatment. Patients’ participation in the trial will end with the last follow-up visit.

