## Assessment

### Clinical measures

The assessments and the procedures performed during the pre-screening, screening, baseline, treatment period and follow-up visits are summarized in Table 2.

**Table 2 Tab2:** Schedule of assessments and procedures

Study period	Pre-treatment		Treatment					Follow-up				
Visit	PS	SV	1	2	3	4	5	6	7	8	9	10
Week	−1		1					2	3	5	9	14
Day^a^		−10	1	2	3	4	5	12±2	19±2	33±4	61±4	95±7
*Assessments*			*Screening and consent*									
Informed consent for pre-screening	•											
ASRS-v1.1	•											
WURS-K	•	•										
Informed consent for clinical trial		•										
In-/exclusion criteria		•										
SCID-5-CV		•										
SCID-5-SPQ^b^		•										
SCID-5-PD^c^		•										
AUDIT		•										
DUDIT		•										
WST		•										
Functional level rating scale		•										
Physical and neurological exam		•										
Medical and psychiatric history		•										
Treatment status		•										
Concomitant medication			•^d^									
Urine drug test			•^d^									
Urine pregnancy test			•^f^									
Randomization			•^d^									

			*Intervention*									
Active/sham tDCS			•	•	•	•	•					

			*Efficacy*									
CAARS-S-SR		•	•^d^				•^e^	•	•	•	•	•
CPT			•^d^				•^e^		•			•

			*Safety*									
tDCS safety screening		•										
BDI-II		•	•^d^				•^e^	•	•	•	•	•
CRQ			•^e^	•	•	•	•^e^					
(S)AE (only during active/sham tDCS)			•^e^	•	•	•	•^e^	•				

			*Social functioning and quality of life*									
AAQoL			•^d^				•^e^	•	•	•	•	•
SCL-90-S			•^d^				•^e^	•	•	•	•	•
PSQI			•^d^				•^e^	•	•	•	•	•

			*Other*									
Demographics		•										
CGI-S			•^d^				•^e^	•	•	•	•	•
CGI-I							•^e^	•	•	•	•	•
Blinding check			•^e^				•^e^					

*PS* pre-screening, *SV* screening visit

^a^Related to randomization

^b^Screening questions for BPD only

^c^Inquiring of the positively screened items from the BPD section only

^d^Before active/sham tDCS

^e^After active/sham tDCS

^f^For females of child-bearing potential

In the context of the pre-screening, the German Adult ADHD self-report scale (ASRS-vI.I [33]) symptom checklist, for evaluation of current symptoms, and the short form of German Wender Utah Rating Scale (WURS-K [34]), for retrospective assessment of symptoms in a participant’s childhood, is filled out online by those interested in participating.

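### New adverse events and SAEs are collected only to day 7 after treatment, before the day-14 primary endpoint and 83 days before the last visit

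*Protocol article*

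**What the plan says.** The section on safety aspects and the data safety monitoring board sets the collection window: adverse events and SAEs "will be collected during treatment period and up to the first follow-up visit after treatment period". Table 2 agrees in its marks: the event row is ticked at visits 1 to 5 and visit 6, and at none of visits 7 to 10. The label of that row is narrower and reads "S)AE (only during active/sham tDCS".

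The study timeline section says that "five visits are scheduled at day 7, 14, 28, 56, and 90 after the end of treatment" and that "Patients’ participation in the trial will end with the last follow-up visit".

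The safety section also explains why the BDI-II is measured during treatment and follow-up: "due to the theoretical risk of worsening or new development of depressive symptoms". It gives the reason: "This risk arises as the electrode placement in our study is opposite to the usual placement in depression treatment". Of events already on record it says: "S)AE will be followed up until complete recovery and/or patient’s status is stable".

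On duration of effect, the Background says: "We hypothesize that the benefits will persist for at least two weeks after the end of the stimulation". The abstract and the statistical analysis section add a repeated-measures analysis to day 90 if the day-14 comparison is significant. The incidence of clinically relevant adverse findings is listed among the secondary endpoints compared between arms.

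**The concern.** The window for new events is shorter than the period over which the plan expects the intervention to act. A plan that looks for benefit two weeks after stimulation, and conditionally up to three months after, has reason to allow for harm over the same period. Here the plan itself names a possible harm that need not be confined to the days of stimulation.

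At stake is the between-arm safety comparison. A psychiatric admission, a suicidal act or any other SAE starting after visit 6 has no stated route into the adverse event data. The comparison of adverse findings would then describe the treatment week and the week after it, while the efficacy results may describe three months.

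Separately, the Table 2 label could lead a site to stop asking about events at visit 5, although the row's own mark and the safety section both extend to visit 6.

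**Working it through.** **Inputs.** Last treatment session on study day 5. Follow-up visits 7, 14, 28, 56 and 90 days after treatment (study timeline). Table 2 study days 12±2, 19±2, 33±4, 61±4 and 95±7. 250 patients randomised 1:1, so 125 per arm.

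**Reproducing the visit days.** 5 + 7 = 12, 5 + 14 = 19, 5 + 28 = 33, 5 + 56 = 61, 5 + 90 = 95. All five match Table 2.

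**Length of the gap.**
- Nominal: 95 − 12 = 83 days.
- Shortest within visit windows: (95 − 7) − (12 + 2) = 74 days.
- Longest: (95 + 7) − (12 − 2) = 92 days.
- Share of the 90-day follow-up: 83/90 = 92%. Share of the 95 study days: 83/95 = 87%.

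**Position relative to the primary endpoint.** 19 − 12 = 7 days nominally. With visit windows, (19 − 2) − (12 + 2) = 3 to (19 + 2) − (12 − 2) = 11 days. Collection closes before the primary endpoint visit in every case.

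**Spacing of the later visits.** Day 28 to 56 is 28 days, and day 56 to 90 is 34 days. A questionnaire given at those visits is the only scheduled contact over each interval.

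**What each provision captures after visit 6.**

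| Provision | After visit 6 |
|---|---|
| Adverse event and SAE collection | Ends at visit 6 |
| Follow-up of recorded events to recovery or stability | Continues, but only for events already captured |
| BDI-II, CGI-S, CGI-I, SCL-90-S | Scores at each attended visit to day 90 |
| Changes in medication and other treatment | Registered, but not as adverse events |

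None of the four records a new event as an event.

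**Illustration in events.** The documents give no event rate. As an assumption, take a constant hazard over 95 days with total risk p. Then h = −ln(1 − p)/95, expected events per arm are 125p, and those inside the window are 125 × (1 − exp(−12h)).

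| p | Expected per arm | Inside window | After window |
|---|---|---|---|
| 1% | 1.25 | 0.16 | 1.09 |
| 2% | 2.50 | 0.32 | 2.18 |
| 5% | 6.25 | 0.81 | 5.44 |
| 10% | 12.50 | 1.65 | 10.85 |

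Under a constant hazard the share after the window is simply the calendar share, about 87%. If events cluster around stimulation, the share is smaller.

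**The case against.** The strongest reply is that the named risk is watched to day 90. The safety section assigns depression severity and suicide risk to the BDI-II at the follow-up visits, Table 2 lists the BDI-II under safety at visits 6 to 10, and it is a secondary endpoint. CGI and SCL-90-S are taken at the same visits, and treatment changes are registered throughout, so a depressive episode that led to new treatment should leave a trace. This stands. A reader might infer that depression goes unobserved after day 7, and the document does not support that. It also calls the risk theoretical, so it should not be presented as an established hazard of this trial.

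Four further inferences would go too far:
- That the committee is blind to late harm. It reviews accumulated study data on safety, which is not limited to adverse event listings, and nothing excludes the BDI-II. What it would lack is late event reports.
- That 92% of events are lost. The figure counts days.
- That the plan hypothesises a 90-day effect. The firm hypothesis is at least two weeks, and the longer period is monitored and tested conditionally.
- That the claim of a low side-effect risk would rest on two weeks of data. That claim is a discussion sentence about what positive results would offer, and the safety evidence also includes BDI-II to day 90.

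What the reply leaves open is the event itself. A scheduled self-report score is not a record of an admission or suicidal act between visits. A patient who drops out after such an event gives no later score, and the treatment-change record also depends on contact. Analysing BDI-II scores by ANCOVA, as the plan does for metric safety endpoints, can bury a few severe cases in a mean difference. Non-depressive SAEs are not the target of any of these measures.

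Nor is this merely detail that a condensed article leaves out: the closing visit is stated in the text and marked in the table.

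**Conclusion.** The point holds as a limited weakness in safety ascertainment. New adverse events and SAEs are collected to study day 12 of 95. The remaining 83 days (74 to 92 with visit windows) have no such collection, and the window closes about a week before the primary endpoint. Depressive symptoms are monitored in that period, but new-onset SAEs and psychiatric events are not recorded as events.

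How many events this would miss cannot be derived from the documents; the event table above rests on an assumed constant hazard. The primary analysis, sample size and power do not depend on the point. The Table 2 label is a wording error that adds no weight to the design criticism but does need correcting. The change is worth making because it is cheap and closes a gap the plan's own reasoning exposes.

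**What to change.** 1. Record SAEs and new or worsening psychiatric adverse events at visits 7 to 10, to day 90 after treatment. For these events the gap falls from 83 days to 0.
2. Include them in the Data Monitoring Committee's review and in the between-arm comparison of adverse findings. Report events to visit 6 and events after it separately as well as together.
3. Reconcile the Table 2 row label with its own visit 6 mark and with the safety section.

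Cost: a protocol amendment and modest extra reporting at four visits that already take place. The article does not describe the eCRF forms, so the database effort is an assumption, though it should be small. Some late events will be unrelated to stimulation; the sham arm gives the comparison for these. Late data would be less complete for patients already enrolled: 28 of the planned 250 at submission, leaving 250 − 28 = 222 still to come at that time. The date from which the extended window applies should be stated so that the two periods can be told apart.

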## Discussion

Here, we report on the design and rationale of a clinical trial conceived to investigate the efficacy of anodal tDCS over the right DLPFC in reducing ADHD symptoms as an alternative or add-on therapy to stable ongoing treatment compared to sham stimulation. There is a lot of evidence that tDCS can lead to an improvement in ADHD symptoms; however, it is still unclear how it can be used in routine clinical practice. To our knowledge, this study represents the first attempt to investigate the effect of tDCS on ADHD symptoms in adults systematically in a multi-center study design.

Over last years, several small tDCS studies with heterogeneous study designs have been conducted in patients with ADHD. The majority of these studies have been conducted in pediatric ADHD patients, presumably due to the high tolerability and relatively low side effect profile of tDCS [50]. Based on the dysfunction findings in fMRI studies conducted in ADHD over the last two decades [16], most of them used tDCS in either one or five sessions targeting mostly DLPFC. Meta-analyses of tDCS effects, mostly over DLPFC, show small effect sizes for improved cognition [23, 51]. However, only a small number of studies have measured clinical improvement in ADHD patients using tDCS, with inconsistent findings [50]. The authors of a meta-analysis of 10 pediatric and 4 adult tDCS studies summarize that a conclusive result is hampered by heterogeneity in stimulation protocols, sample age, and cognitive measures. Therefore, the authors call for larger, double-blind, randomized, controlled trials with homogeneous protocols testing both clinical and cognitive outcomes in ADHD [23]. Almost all authors of reviews and meta-analyses on the use of tDCS in ADHD also conclude that the efficacy of tDCS, and especially its clinical benefit on ADHD symptoms, cannot yet be conclusively assessed and further studies with optimized designs are warranted (see as example [52]). With our study, we aim to contribute to gathering more robust data on this.

The intention of this clinical trial is to include both medicated and unmedicated ADHD patients, to investigate the effects of tDCS as an add-on therapy to the treatment adhering to standard ADHD guidelines as well. Thus, the design is primarily intended to reflect clinical reality, because in our opinion the investigation of tDCS as a stand-alone therapy would only be applicable to a small group of clinical patients. Another important point in the preparation of our study was the choice of primary and secondary endpoints. In order to choose measures that are also relevant from a patient perspective, we involved patients and their relatives in this decision. Previous studies mostly investigated either the effects of tDCS on neuropsychological symptoms or clinical symptoms [52], however we decided to survey both aspects, including quality of life parameters in our study, which was also supported by the patients.

Concerning electrode placement, stimulation intensity, and frequency, the methodological decision was based on the above mentioned evidence. The lateralization of the excitatory electrode over right DLPFC was supported by neuroimaging study of our own working group, which indicated that prefrontal hypo-activation is more pronounced on the right side [31]. The selection of the stimulation parameters was based on the previous pilot study by Cachoiera et al. [30], which showed significant lower self-reported ADHD symptoms after active tDCS in comparison with sham stimulation. In order to measure short-term and also possible mid-term effects, we significantly extended the follow-up period with visits up to day 90 after the intervention. Potentially observed long-lasting effects would be instrumental in clinical implementation of tDCS in ADHD.

In summary, positive results of this parallel, randomized, double-blinded, sham-controlled, multi-center trial would expand the treatment options for adult ADHD patients with an alternative or add-on therapy to psychostimulants with a low risk for side effects. Detailed reporting of study protocols is intended to increase transparency in clinical research.

### Trial status

Enrollment for the study began in September 2022. At the time of submission, we have enrolled 28 participants at two study sites (Leipzig, Wurzburg).
